#### Sample size calculations

The prospective power analysis was based on data from previous studies from our group using intravital video-microscopy. This analysis indicated that a sample size of 16 subjects per group would have 80% power at the 5% significance level to detect a difference of 7-capillaries/mm^2^ (the standard deviation) during PORH between groups. The calculations were made using classical power calculations with the formula.$$ n = f(\alpha ,\beta ) \cdot \frac{{2s^{2} }}{{\delta^{2} }} $$where *α* is the significance level, *β* is the power of the test, *f* (α, β) is a value calculated from *α* and *β* (in this case 7.9), *δ* is the difference in means that we should be able to detect, and *s* is the standard deviation determined in previous studies.

#### Statistical analysis

The results will be presented as the mean ± SD. For values that do not follow a Gaussian distribution, the medians (25th–75th percentiles) will be presented (Shapiro–Wilk normality test). The results will be analyzed using either two-tailed unpaired Student’s *t*-tests or repeated measures ANOVAs when appropriate. The independent (unpaired) *t* test will be used because we will compare two unrelated groups, in which the participants (healthy individuals or patients with IE) in each group are different. P values <0.05 will be considered statistically significant. The statistical package to be used for the statistical analyses is Prism version 6.0 (GraphPad Software Inc. La Jolla, CA, USA).

Clinical and laboratory data will be shown descriptively. The correlations between the intervention study results (capillary density and microvascular reactivity) and features of the disease, such as the number of days of presentation, presence of embolic complications and etiological agent, will be determined using Pearson’s test if the data are found to be of normal distribution (parametric). If the distribution is not normal (non-parametric), Spearman’s test will be used for the analysis.

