## Introduction

Infective endocarditis (IE) is a disease with a high mortality rate that can potentially lead to severe complications. Its clinical presentation is dynamic and variable; it is dependent on patient age, the presence of comorbidities (especially underlying valvular heart disease), the causative microorganism and the presence of complications. In recent years, there has been a change in its epidemiological profile, especially in developed countries. Although younger patients with rheumatic valve disease were the predominant population affected by IE, in the last two decades, older individuals and healthcare-associated infections (including those related to intracardiac devices, valve prosthesis and hemodialysis) and a staphylococcal etiology have become more frequent [1, 2]. However, in developing countries, patients with rheumatic valve disease account for a third of all IE cases, and the *viridans* group streptococci is the causative agent in a third of all IE cases [3].

Infective endocarditis is a systemic disease involving the vascular system and is often accompanied by bacteremia or fungaemia. Therefore, it results in a septic state. In addition, acute heart failure or acute-on-chronic heart failure commonly complicates left-sided IE due to valve destruction, which leads to acute valvular regurgitation. Indeed, the most common indication for valve replacement surgery is severe heart dysfunction not amenable to pharmacologic intervention [1–3]. Considering the severity and increasing incidence of IE, it is important to better understand the pathophysiology of the endocarditis syndrome. The use of noninvasive techniques in the early diagnosis of IE and its complications may prove useful. In fact, the evaluation of systemic microvascular reactivity has proven to be very helpful in the investigation of the pathophysiology of cardiovascular and metabolic disorders [4, 5] as well as sepsis [6].

Abnormalities in the microcirculation have been demonstrated through microvascular rarefaction to be present in diseases such as arterial hypertension, diabetes, obesity and metabolic syndrome [5, 7–11]. Moreover, impaired systemic microvascular function, characterized primarily by capillary rarefaction in the skin, has been demonstrated in individuals with increased coronary artery disease risk [12, 13].

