#### Study variables

The variables to be included are as follows: demographic data (sex, age and ethnicity), previous medical history (comorbidities, previous valvular diseases and cardiac interventions), medications in use, data regarding the episode of IE (date of onset, causative pathogen, affected valve or structure, echocardiographic data, local and systemic embolic and non-embolic complications, antibiotic and surgical treatment) and laboratory data (CRP, ESR and creatinine levels).

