#### Intervention

The evaluation of microvascular endothelial function in patients with infective endocarditis will be performed using laser speckle contrast imaging and skin video-capillaroscopy. These results will be compared to those previously obtained from age- and sex-matched healthy volunteers [13]. The systemic microvascular data obtained from this group of healthy volunteers will be used as reference microcirculatory values of individuals free of systemic diseases. None of the healthy volunteers presented with arterial hypertension, diabetes, dyslipidemia or any other systemic pathology.

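### The between-group test uses neither age nor sex, although the controls' results already exist and balance on these two variables depends on later selection

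*Protocol article*

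**What the plan says.** All references are to the protocol article.

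- **Source of the controls (Intervention):** "These results will be compared to those previously obtained from age- and sex-matched healthy volunteers". Their data serve as the benchmark for people without systemic disease. The Abstract also describes a control group matched on sex and age. Neither place says whether matching is by pair or by group, or by what rule.
- **Patients (Study participants and recruitment):** enrolment is consecutive and prospective, from age 18, with no upper age limit stated.
- **Test (Statistical analysis):** the method is the t-test ("The results will be analyzed using either two-tailed unpaired"), with a repeated measures ANOVA as the alternative where that fits. The reason given for the unpaired form is that this "test will be used because we will compare two unrelated groups, in which the participants (healthy individuals or patients with IE") are not the same people in the two groups. No pairing and no covariate is named.
- **Data held (Study variables):** the list for patients includes "demographic data (sex, age and ethnicity").
- **Size (Sample size calculations):** the plan states that "a sample size of 16 subjects per group would have 80% power at the 5% significance level". The target is a gap of one SD, 7 capillaries/mm², in the post-occlusive hyperemia test.

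**The concern.** This is a non-randomised comparison with about 16 people per group. Age and sex are the two variables on which the groups are said to be matched. The control measurements were taken before the patients' ages and sexes were known, so balance can come only from selecting or subsampling volunteers afterwards. That may work, but nothing in the design guarantees it.

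The analysis then leaves both variables out, with one of two consequences:

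- **Balance is imperfect.** The part of the difference due to age or sex is attributed to endocarditis. Its direction depends on which group is older and on how the outcome changes with age, neither of which the article gives.
- **Balance is good.** There is little bias, but outcome variation that age and sex could explain stays in the error term, and the interval is wider than it need be.

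**Working it through.** **Inputs from the article:** difference 7 capillaries/mm², equal to one SD, so SD = 7; two-sided 5% level; 80% power; 16 per group; multiplier 7.9 ("in this case 7.9").

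**1. The plan's own figure.** n = 7.9 × 2 × 7² / 7² = 15.8, rounded up to 16. The stated size reproduces, for two independent groups. With the t distribution (30 df, noncentrality √(16/2) = 2.83), power at n = 16 is 78.1%. This is the baseline for the comparisons below.

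**2. Balanced groups: what adjustment could gain.** The article gives no figure for the outcome variance explained by age and sex, so R² is assumed. A model with intercept, group, age and sex has 32 − 4 = 28 df. The noncentrality becomes 2.83/√(1 − R²), and the unadjusted SE is larger than the adjusted one by a factor 1/√(1 − R²).

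| Assumed R² | SE ratio | Adjusted power |
|---|---|---|
| 0 | 1.00 | 77.9% |
| 0.05 | 1.03 | 80.0% |
| 0.1 | 1.05 | 82.1% |
| 0.2 | 1.12 | 86.3% |
| 0.3 | 1.20 | 90.4% |

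If age and sex explain nothing, the two degrees of freedom cost 0.2 points of power (78.1% to 77.9%).

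**3. Unbalanced groups: what the unadjusted test could get wrong.** Age slope and mean age gap are also assumed. Bias in SD = slope per decade × gap/10; bias in capillaries/mm² = 7 × that; noncentrality under no true difference = bias in SD × √8. The actual type I error of the nominal 5% test is then:

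| Slope (SD per decade) | Gap 2 years | Gap 5 years | Gap 10 years |
|---|---|---|---|
| 0.1 | 0.14; 5.0% | 0.35; 5.2% | 0.70; 5.9% |
| 0.2 | 0.28; 5.1% | 0.70; 5.9% | 1.40; 8.5% |
| 0.3 | 0.42; 5.3% | 1.05; 7.0% | 2.10; 13.0% |

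Each cell gives bias in capillaries/mm², then type I error. The largest bias is 2.1/7 = 30% of the target difference.

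**4. The two benefits do not add.** Step 2 assumes balance and step 3 assumes imbalance. When groups differ in age, the adjusted SE is inflated by the correlation between group and age. For a gap of one within-group SD of age and equal groups, the squared correlation is 1/(1 + 4) = 0.2. With R² = 0.1 the SE ratio, adjusted to unadjusted, is √(0.9/0.8) = 1.06. Bias is removed, at an SE about 6% larger.

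**The case against.** The strongest defence is that the plan is coherent for group (frequency) matching. The sample size is for independent groups, the analysis calls the groups unrelated, and the volunteers are presented as a reference set. Under group matching an unpaired comparison is acceptable. That stands, and it limits the point to the missing adjustment.

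Several stronger readings are tempting but unsupported:

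- **That a paired test was required and the stated reason is an error.** It is true that matched pairs are always different people, so the reason given would not rule out pairing. But the article never states individual pairing. Had there been 16 true pairs, the unpaired test would be conservative rather than invalid: by simulation its type I error is 3.0% at an assumed within-pair correlation of 0.2 and 0.8% at 0.5. At 0.1 or less there is no meaningful loss of power (79.2% unpaired, 79.6% paired at 0.1).
- **That matching is wasted.** Real matching balances age and sex whichever test is used.
- **That the volunteers cannot match these patients, or were matched to some other group.** A finished pool can be subsampled. The Introduction cites the same reference for a finding that "has been demonstrated in individuals with increased coronary artery disease risk [12, 13"], but what that study matched its volunteers to cannot be told from this article.
- **That controls will be chosen with their results in view.** Those results exist, but the article does not say who selects or what they can see. Blinding of the image readers is stated; it does not cover selection.
- **That age and sex are the only factors controlled.** Diabetes is excluded in patients and absent in controls, and skin flow is divided by mean arterial pressure.
- **That false positives could approach 28%.** This figure (27.8%) needs a shift of 3.5 capillaries/mm², or 0.5 SD. At the slopes above it implies an age gap of 0.5/0.3 to 0.5/0.1 decades, about 17 to 50 years, which is implausible for groups called age-matched.

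A condensed article may also leave the matching rule to the full protocol, so its absence is not itself the fault. The unadjusted test, however, is stated outright and with a reason.

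**Conclusion.** The point holds in a limited form and the analysis should be changed. As written, the comparison uses neither matching variable, while the controls' results predate the patients' enrolment and balance is not guaranteed. The article shows no actual imbalance, so the size is unknown. Under the assumed ranges, the harm is either a bias of 0.14–2.1 capillaries/mm² with type I error of 5–13%, or, with balanced groups, forgone power of about 4 to 12 points (78.1% against 82.1–90.4%). At the low end of each range the effect is negligible. The sample size arithmetic is sound and is not part of this point.

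**What to change.** 1. For each between-group outcome with one value per person, replace the unpaired t-test with a linear model, outcome = group + age + sex, and report the adjusted difference with its 95% CI.
2. For outcomes assigned to repeated measures ANOVA, use a repeated-measures (mixed) model that includes age and sex; the one-row-per-person model in item 1 does not handle these.
3. Include all eligible volunteers of the earlier study, or select them by a written age and sex rule applied without access to their microvascular results.
4. State whether matching is by pair or by group, and report age and sex by group.

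Cost: two degrees of freedom, revised wording, and software that fits these models (whether the named package does so should be checked). No new patient measurements are needed. Age and sex are listed for patients; for the volunteers, their description as matched implies that both are on record, which should be confirmed. If the groups differ in age, the adjusted SE may be somewhat larger than the unadjusted one, and the adjustment relies on the two age ranges overlapping.

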## Limitations and strengths of the study

The restricted number of participants due to limitations regarding the inclusion of critically ill patients with a diagnosis of infective endocarditis.The heterogeneity of patients presenting with IE, which is due to several differences, including underlying diseases, such as chronic valvular disease (present or not) and chronic renal failure (present or not and hemodialysis dependent or not); etiologic agents, which may be more aggressive, such as *Staphylococcus aureus*, or more indolent, such as *viridans* group streptococci; the type of structure involved, such as the mitral or aortic valves and the tricuspid valve (associated with devices or not); the type of treatment received by the patient (surgical vs. non-surgical); and the duration of treatment at the time of the study protocol.The main strength of the present study is the assessment of the usefulness of laser-based noninvasive techniques in the evaluation of systemic microcirculation and its role in the early diagnosis of infective endocarditis and, possibly, its complications.

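### Etiological agent, an unordered category with no stated coding, is assigned to Pearson's or Spearman's correlation, so with three or more organisms the result depends on arbitrary number codes

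*Protocol article*

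**What the plan says.** The second paragraph of Statistical analysis (Protocol article) sets out one analysis for the clinical correlates: "The correlations between the intervention study results (capillary density and microvascular reactivity) and features of the disease". Three features are given as examples, "such as the number of days of presentation, presence of embolic complications and etiological agent, will be determined using" one shared rule: "Pearson’s test if the data are found to be of normal distribution (parametric"), and otherwise "If the distribution is not normal (non-parametric), Spearman’s test will be used for the analysis".

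No other method is assigned to organism. The unpaired t-test and repeated measures ANOVA appear in the preceding paragraph, where the t-test is justified by the comparison of healthy individuals with patients.

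Study variables lists the organism among the episode data simply as an item to record: "date of onset, causative pathogen, affected valve or structure". It defines no ranking or grouping. The nearest thing to an order is in Limitations and strengths of the study, which mentions "etiologic agents, which may be more aggressive, such as" Staphylococcus aureus, and contrasts them with more indolent viridans streptococci. Those are two examples of patient heterogeneity. They are not an analysis coding, and they place no other organism.

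**The concern.** Pearson's coefficient needs numbers and Spearman's needs ranks. Days of presentation supplies both. Organism supplies neither, so someone must number the organisms before either coefficient can be computed. With three or more organisms there are several non-equivalent ways to do that, and nothing in the article chooses among them.

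Two things follow. The coefficient does not measure any property of the patients that a reader could interpret. And because the coding is not fixed, it could be settled after the data are seen, without any departure from the text. At stake is the only stated analysis that links the microvascular findings to the causative organism.

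**Working it through.** **Inputs.** From Sample size calculations: "a sample size of 16 subjects per group would have 80% power at the 5% significance level", with the detectable difference equal to the SD (7 capillaries/mm²) and f = 7.9. The article gives no distribution of organisms, so four organisms with four patients each is an assumption, chosen to total 16 patients. The measurements below are made up for illustration.

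**The plan's own figure.** n = 7.9 × 2 × 7²/7² = 15.8, rounded up to 16. The sample size reproduces. The point does not depend on it; it only indicates how many patients are available for the correlations.

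**One dataset, different codings.** Values by organism:

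- A: 62, 70, 75, 81 (mean 72.00)
- B: 85, 90, 96, 102 (mean 93.25)
- C: 70, 78, 83, 88 (mean 79.75)
- D: 92, 97, 104, 110 (mean 100.75)

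Pearson's r = Sxy/√(Sxx·Syy). The total sum of squares is Syy = 2737.94. For codes 1 to 4 with four patients each, the centred codes are -1.5, -0.5, 0.5 and 1.5, so Sxx = 4 × (2.25 + 0.25 + 0.25 + 2.25) = 20 and √(Sxx·Syy) = 234.0.

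- Coding A=1, C=2, B=3, D=4: Sxy = 4 × (-1.5×72 - 0.5×79.75 + 0.5×93.25 + 1.5×100.75) = 199.5, so r = 199.5/234.0 = +0.85 (P = 0.00003).
- The same coding reversed: r = -0.85, same P.
- Coding B=1, A=2, D=3, C=4: Sxy = 4 × (-1.5×93.25 - 0.5×72 + 0.5×100.75 + 1.5×79.75) = -23.5, so r = -23.5/234.0 = -0.10 (P = 0.71).

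Over all 24 codings:

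| Method | Coefficient | P value |
|---|---|---|
| Pearson | -0.85 to +0.85 | 0.00003 to 0.71 |
| Spearman | -0.88 to +0.88 | 0.000007 to 0.67 |
| One-way ANOVA | not affected by coding | 0.0009 |
| Kruskal-Wallis | not affected by coding | 0.008 |

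Either correlation gives P<0.05 in 10 of the 24 codings (42%). Assigning the same 16 values to three organisms (6, 5 and 5 patients) gives r from -0.66 to +0.66; five organisms (4, 3, 3, 3 and 3) give -0.79 to +0.79.

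**Long-run behaviour (simulation, Spearman, four organisms of four).** With no true effect, one coding fixed in advance is significant in about 5% of datasets. The most favourable of the 24 codings is significant in 23% to 26%, depending on the run. When one organism differs by 1.5 SD, some codings are significant and others are not in 72% to 76% of datasets. With three organisms (6, 6 and 4), the corresponding figures are 14% and 82%, so the problem does not hinge on four groups.

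**The yes/no feature.** Splitting the same 16 values 10/6 and coding the split 0/1, 1/2 or 5/-3 gives |r| = 0.546 and P = 0.0285 each time. Since t = r√14/√(1 - r²) = 0.546 × 3.742/0.837 = 2.44 on 14 df, this is exactly the unpaired t-test (P = 0.0285). For two groups, recoding can change only the sign.

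**The case against.** The strongest defence is that the coefficient is uninterpretable only with three or more unordered categories. If organism is reduced to two groups, or given an ordinal score in advance, a correlation is legitimate. The article contrasts aggressive with indolent agents and singles out staphylococcal disease in the Introduction, so such a coding may exist in the full protocol or analysis plan, which are not shown. This lowers the certainty of the defect but does not remove it: the article names the method outright, records organism without grouping, and states no coding.

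Four stronger readings are tempting, and the document does not support them.

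- A reader might infer that the analysis of embolic complications is also invalid. It is not. Pearson on a 0/1 variable reproduces the unpaired t-test, and Spearman is then a rank-based comparison of two groups.
- A reader might infer that the normality rule breaks the analysis. The text does not say which variable is to be checked, and it can be read as the microvascular measure. Applied to a 0/1 variable, it would merely lead to Spearman. The wording is awkward, but no wrong result follows for a two-group feature.
- A reader might take about 25% as the plan's false-positive rate. That figure describes someone who tries every coding and keeps the best, and nothing in the article suggests such a search is intended.
- A reader might infer that a declared staphylococcal hypothesis is compromised. The Introduction states a background expectation of sepsis-like findings, with no planned test attached.

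It is also fair to say that the remedy will not rescue a small sample. In the 1.5 SD scenario, Kruskal-Wallis had only about 32% power.

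**Conclusion.** The point holds for etiological agent alone. The article prescribes a method that does not fit the variable as recorded, and with three or more organisms the sign, size and significance of the result follow from the numbering. The size shown (rho from -0.88 to +0.88 on one dataset) rests on assumed data and an assumed organism mix; the dependence on coding itself does not. The analysis is secondary, and neither the patient-control comparison nor the 16 per group changes. It should be fixed, but it is not a threat to the main result.

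**What to change.** Keep Pearson or Spearman for quantities such as days of presentation. For etiological agent, replace the correlation with a comparison of microvascular results across organism groups by one-way ANOVA or Kruskal-Wallis. Alternatively, pre-specify one two-group contrast, such as Staphylococcus aureus versus all other agents, which the article's own discussion of heterogeneity motivates. State the grouping before the data are analysed, and label the result exploratory because groups will be small at about 16 patients.

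For embolic complications no correction is needed. Reporting the difference between patients with and without them, with a 95% CI, would be an optional and clearer presentation.

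The cost is a change of wording in the analysis section. It needs no new data or additional patients.

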### Discussion

Infective endocarditis remains a disease with high mortality (approximately 15–20% among patients who undergo surgery) and morbidity despite improvements in diagnosis and timely surgical intervention [1, 2]. It is associated with persistent bacteremia or fungaemia and consequent sepsis. Studies evaluating the microcirculation in patients with endocarditis are scarce in the literature. Only one French study, in which nailfold capillary microscopy was used to study twenty-six patients with IE, showed significant correlations of the number of capillary abnormalities with systemic involvement and immunological disturbances [20]. However, the authors concluded that due to the lack of specificity, nailfold capillary microscopy could not be regarded as a useful tool for the diagnosis of infective endocarditis. Another important issue to consider is the relatively frequent occurrence of severe valvular regurgitation leading to acute heart failure in left-sided IE, which may further compromise microcirculation and tissue perfusion, possibly modifying the response of the microvascular endothelium to sepsis.

Several studies have demonstrated the central role of microcirculation in the delivery of nutrients and oxygen to tissue cells and, therefore, in determining adequate organ perfusion [29, 30]. In sepsis and septic shock, macro and microcirculatory disturbances both contribute to the development of organ failure. Macro and microcirculatory mismatch in septic patients may lead to inappropriate treatment measures and higher mortality [31]. Microcirculation and its effects are a focus of present and future research that aim to improve diagnostic and treatment strategies. Moreover, it has recently been demonstrated that treatment at an early stage of microvascular dysfunction may be most effective for delaying or reversing the disease processes, thus improving the outcome and survival of patients at risk for pulmonary vascular disease [32]. The authors also suggested that this knowledge may be applied toward microvascular dysfunction observed in the skin [32].

In sepsis, microvascular blood flow is disturbed by endothelial dysfunction, which leads to a reduction in flow or no flow at all to some capillary beds, while other beds have above normal flow, even surpassing tissue metabolic demands. This microvascular perfusion heterogeneity results in tissue hypoxia. Endothelial dysfunction in sepsis also results in an inflammatory response, which together with tissue hypoxia, leads to organ failure and mortality [31, 33]. Intravenous fluids and vasoactive agents are important measures in the treatment of sepsis. Intravenous fluids may improve microvascular perfusion, increasing the proportion of perfused capillaries and decreasing flow heterogeneity. However, systemic circulatory changes may be relatively independent of changes in the microcirculation [33, 34].

Our study proposes to evaluate the baseline cutaneous functional capillary density and capillary recruitment (capillary reserve) in patients with IE using PORH. Capillary rarefaction and heterogeneous capillary flow may be shown [18]. In addition to using a laser speckle contrast imaging system, whether microvascular reactivity is normal may be demonstrated with acetylcholine, an endothelium-dependent vasodilator, and sodium nitroprusside, an endothelium-independent vasodilator drug. The results of these studies may be helpful in providing information on the systemic involvement of microcirculation in infective endocarditis.

